#### Caregiver burden and quality of life will be assessed using

(i) the Zarit Carer Burden Scale [48]; and (ii) the Assessment of Quality of Life (AQoL) [49].

### Randomization

After baseline assessment, participants will be randomly allocated into the exercise or control groups. Randomization will be by computer generated random numbers table, with group allocation on a folded piece of paper in an opaque envelope, packed by a staff member independent of the project team. A research assistant independent of the assessors will identify group allocation, and communicate with the participant and their carer as to which group they are in, and make arrangements for the next stage of the project. In this way, assessors will be blind to the group allocation-randomization process at the time of the baseline assessment.

### Intervention Group and Control Group Activities

**The control group **will continue with "usual care" for the subsequent six months without interruption, including all activities and service use recommended by treating health professionals. In addition, participants in the control group will receive a home programme involving six home visits for the six month period by an Occupational Therapist, to provide an information/education and support programme. Topics to be covered in the programme include issues around diagnosis; community services; occupational performance (including issues around grief and losses); and environmental safety and aids. The programme will avoid any messages encouraging any change in activities that may influence balance and mobility performance. Control participants will receive phone calls from the Occupational Therapist to follow up on issues raised in the home visits between home visits.

**The intervention group **will participate in a tailored (individualised) home based balance exercise programme, provided by a physiotherapist. This exercise programme is based on an existing home exercise programme (the Otago programme, ), which has been shown to improve balance and reduce falls in older people without cognitive impairment in the community setting [50-52]. The programme has been modified to provide increased support and visits in the early stages of exercising. Appropriate exercises from the Otago programme will be selected by the physiotherapist, and be tailored to balance and mobility problems identified from the assessments. Participants will receive six home visits during the six month duration (two visits in the first month after the baseline assessment, two further visits in the second month, then two more home visits four to six weeks apart for the remaining times). An exercise booklet will be provided by the physiotherapist to each participant or carer to give illustrations and instructions for the participant to continue the exercise programme at least five times a week. In between visits, the physiotherapist will contact participants by telephone (five phone calls during the six month duration). Adherence to the programme will be monitored by daily completion of an exercise diary. All participants will also continue to receive 'usual care'.

### Follow Up Assessments

Six months after the initial assessment all participants will have all baseline measures repeated by an assessor blind to group allocation. Measures will be repeated six months later (ie 12 months after initial assessment) to determine sustained benefits from the programme.

### Focus Groups

A randomly selected sub-sample of 20 participants from the exercise programme and their caregivers will be invited to participate in focus groups to discuss issues about falls, balance problems, positive and negative aspects of the exercise programme, and other relevant factors influencing participation and outcomes. Data from the focus groups will be recorded, transcribed, and thematically analysed to provide qualitative data informing future recommendations.

### Safety

All assessments will be undertaken by an experienced physiotherapist, providing close supervision during all tasks. In addition, a safety harness will be used for several of the NeuroCom Balance Master™ assessments, which will allow the participant freedom of movement to elicit balance reactions, but will prevent them from falling in the case of overbalancing. The home exercise programme is based on a home exercise programme that has been shown in a number of studies of older people with increased falls risk to be safely implemented, and to reduce falls [50,52]. The frequency of home visits in this study is slightly increased on the successful "Otago" programme (4 visits), aiming to maximise safety with increased visits particularly in the first 6–8 weeks of the programme. The personalized balance exercise programme will be tailored to each individual by an experienced physiotherapist. The exercise prescription and implementation will take into account participant safety.

### Ethical Considerations

Participants will be reassured that their decision as to whether or not they participate in the study is voluntary, and that participation will not influence their usual treatment. Written informed consent will be obtained. If the person with Alzheimer's disease is unable to provide informed consent (as determined by CDAMS records or general practitioner records) to participate (or to continue participation), their next of kin or their caregivers (person responsible) will be asked to provide written consent. The name and contact details of all participants and any information obtained in connection with this research that can identify individual participants will remain confidential and will be used only for the purpose of the research. In any publication, information will be provided in such a way that no individual participant can be identified. All records collected for this research will be kept in a secure place. All records will be archived and retained for a minimum of seven years according to the ethics protocol. At the end of this period, paper-based records will be shredded, and electronically stored data will be erased.

Ethics approval has been obtained from the Melbourne Health Human Research Ethics Committees (HREC 2008.004/Approval Date: 16-Apr-08), and the University Human Ethics Committee, La Trobe University (Application No. 08-011/Approval Date: 30-Jul-08).

### Primary Outcome Measures

Two primary outcome measures have been selected: Limits of Stability (LOS) test (Maximum Excursion measure) (Neurocom Balance Master™) and the Step Test. All other measures will be considered as secondary outcomes. The LOS Maximum Excursion measure is a dynamic balance measure which has been shown to be a sensitive measure of balance impairment, and to be responsive to exercise interventions in older populations [38,40,53]. The Step Test is a simple clinical balance measure which is routinely used in clinical practice and research in the field of balance and falls prevention. It has high reliability [42] and is sensitive to change in balance performance in older people with clinical conditions such as Parkinson's disease [54,55] and stroke patients [42,56], and is responsive to change following an exercise intervention [57].

### Sub-study – Longitudinal Change in Balance Performance

The first 64 participants recruited for the primary study and randomised to the control group will undergo complete assessments as described in the primary study, but also have further complete assessments at 18 months and 24 months following the initial assessment. Sixty four age and gender matched healthy participants will also be assessed on the full balance assessment battery at 0, 6, 12, 18 and 24 months for comparison of the rate of change in balance performance in the sample with mild to moderate severity Alzheimer's disease.

### Statistical Analysis

Intention to treat analysis will be used. Balance performance on the two primary outcome measures and the secondary outcome measures will be made using repeated measures ANOVA between the two groups, with variables differing between groups at baseline being used as covariates. Multivariate logistic regression will be used to evaluate factors associated with improved outcomes, including level of adherence to the exercise programme. For the longitudinal sub-study, independent sample *t*-tests will be used to determine differences in balance performance between both groups at each time point.

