**Methods/design:**

Two hundred and fourteen community dwelling participants with mild to moderate severity Alzheimer's disease will be recruited for the randomised controlled trial. A series of laboratory and clinical measures will be used to evaluate balance and mobility performance at baseline. Participants will then be randomized to receive either a balance training home exercise programme (intervention group) from a physiotherapist, or an education, information and support programme from an occupational therapist (control group). Both groups will have six home visits in the six months following baseline assessment, as well as phone support. All participants will be re-assessed at the completion of the programme (after six months), and again in a further six months to evaluate sustainability of outcomes. The primary outcome measures will be the Limits of Stability (a force platform measure of balance) and the Step Test (a clinical measure of balance). Secondary outcomes include other balance and mobility measures, number of falls and falls risk measures, cognitive and behavioural measures, and carer burden and quality of life measures. Assessors will be blind to group allocation.

Longitudinal change in balance performance will be evaluated in a sub-study, in which the first 64 participants of the control group with mild to moderate severity Alzheimer's disease, and 64 age and gender matched healthy participants will be re-assessed on all measures at initial assessment, and then at 6, 12, 18 and 24 months.

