## Background

Dementia is a major worldwide health problem among older people. It is one of the most burdensome conditions, and is a leading cause of disability and mortality in later life [1]. The prevalence of dementia is estimated to be 1.5% of people aged 65 years, and prevalence becomes more common with increasing age, reaching a level of 22% in people older than 85 years [2]. The global prevalence of dementia is forecast to double every 20 years, to 42.3 million in 2020 and to 81.1 million people in 2040 [3]. It is estimated that there will be more than one million people with dementia in the UK by 2025 [4]. The number of people with dementia is expected to triple in the United States by 2040 [5], and in Australia by 2050 [6]. Alzheimer's disease is the most common type of dementia, accounting for 50–70% of all dementias [7,8].

Falls are another major public health issue for the older population, with 30% percent of people aged 65 and over falling once or more each year [9,10]. Even higher falls rates have been reported for people with dementia, with around 42% of a community sample with mild-moderate dementia, and 60% of people with dementia in residential care falling at least once each year [11,12]. Decrease in balance performance is a strong indicator of falls in older people [13,14]. Greater balance and gait disturbances have been found in people with dementia when compared with older people in general [15,16], and these have been shown to occur in relatively early stages of the dementia pathway [17]. These declines in balance and motor performance may explain the increased incidence of falls in people with dementia, and have been shown to be a predictive factor for people with dementia needing permanent skilled nursing facility admission [18]. Increased carer strain has also been reported following a fall by care recipients [19].

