#### Measures of falls and falls risk include

(i) the number of falls in the preceding 12 months will be collected from the participant or carer, based on retrospective recall; (ii) the Falls Risk for Older People (FROP-Com) [46], a detailed falls risk assessment tool evaluating 13 risk factors; and (iii) Physiological Profile Assessment (PPA) [47] abbreviated assessment, evaluating standing balance, hand reaction time, knee joint proprioception, visual contrast sensitivity and quadriceps muscle strength. The FROP-Com and the PPA have been shown to have good retest reliability (FROP-Com intra-rater and inter-tester reliability were 0.93 and 0.81 respectively, and the PPA retest reliability ranged from 0.50 to 0.97), and the FROP-Com to have moderate capacity to predict falls (sensitivity 71% and specificity 56%) [46,47].

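### The 6-month falls count reaches six months back before baseline, and the planned ANOVA treats baseline falls as an occasion, not a covariate, which dilutes the end-of-programme falls effect and loses power

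*Protocol article*

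**What the plan says.** The Abstract lists falls among the secondary outcomes: "Secondary outcomes include other balance and mobility measures, number of falls and falls risk measures". Primary Outcome Measures names Limits of Stability and the Step Test, then adds: "All other measures will be considered as secondary outcomes".

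The section on falls and falls risk defines the measure: "the number of falls in the preceding 12 months will be collected from the participant or carer, based on retrospective recall". Measurements and Procedures applies the listed measures at baseline and at the later assessments. Follow Up Assessments confirms this: "Six months after the initial assessment all participants will have all baseline measures repeated by an assessor blind to group allocation", and then "Measures will be repeated six months later (ie 12 months after initial assessment". No shorter recall period is given for follow-up, and the only diary described records exercise adherence.

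For the analysis, the Statistical Analysis section says that "the secondary outcome measures will be made using repeated measures ANOVA between the two groups". Covariates are to be those variables that happen to differ between groups at baseline.

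**The concern.** Two separate things look wrong.

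- **The recall window.** A 12-month look-back at a 6-month visit counts falls from before randomisation, when the programme can have had no effect. The 6-month visit is the end-of-programme assessment, so the comparison of most interest for falls is pulled towards no effect.
- **The use of baseline falls.** In a group-by-time ANOVA the baseline count is one of the repeated occasions, so the group effect is judged on change from baseline. For a noisy count that is less efficient than adjusting the follow-up count for the baseline count. Baseline falls would become a covariate only if the groups happened to differ on them.

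Falls are a large part of the trial's rationale in the Background and Discussion. A diluted or underpowered falls result could be read as evidence that the programme does not affect falls. The first fault arises in data collection, so later analysis cannot undo it.

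**Working it through.** **1. Recall windows** (falls section and Follow Up Assessments)

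| Visit | Months covered | Share after randomisation |
|---|---|---|
| Baseline | -12 to 0 | none |
| 6 months | -6 to +6 | half |
| 12 months | 0 to 12 | all |

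Write A, B, C and D for the falls in months -12 to -6, -6 to 0, 0 to 6 and 6 to 12. The trial records A+B, B+C and C+D. Three sums do not determine four unknowns, so C cannot be recovered by subtraction. A participant who completes 12 months at least supplies C+D. A participant lost between months 6 and 12 supplies only B+C, which is half pre-randomisation. Sample Size plans for 25% loss, which is 214 - 160 = 54 people. How many would leave after month 6 is not stated.

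**2. Dilution at month 6.** Assume an even fall rate and an effect that starts at month 0:

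apparent ratio = 0.5 × 1 + 0.5 × true ratio

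- True 0.7: 0.5 + 0.35 = 0.85
- True 0.6: 0.5 + 0.30 = 0.80
- True 0.5: 0.5 + 0.25 = 0.75

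**3. Power: inputs.** The plan gives no power figure for falls, so there is none to reproduce.

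- From Sample Size: 80 completers per group.
- From the Background: "around 42% of a community sample with mild-moderate dementia" fall at least once a year, so about 58% have none.
- Assumed: mean 1 fall per year. For a negative binomial, P(0) = (1 + k)^(-1/k). With k = 2.04 this is 3.04^(-0.490) = 0.58, and the variance is 1 + 2.04 = 3.04.
- Assumed: rate ratios of 0.6 and 0.5, and a fall tendency for each person that is the same before and after baseline.

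**4. Power: one clean 12-month window before and one after baseline.** Ranges are over repeated simulations of 800 to 1,500 trials, where available.

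| Analysis | Ratio 0.6 | Ratio 0.5 |
|---|---|---|
| ANOVA group-by-time (t-test on change) | 43–44% | 60–61% |
| Negative binomial, baseline falls as covariate | 56–61% | 81–83% |
| Least-squares ANCOVA on raw counts, baseline falls as covariate | 55–62% | 80–82% |
| Negative binomial, no baseline covariate | 42–43% | 64% |

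The second and third rows agree, and the fourth is close to the first. The gain comes from the baseline covariate.

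**5. Power: the three overlapping windows as planned.** Dispersion 1 / 2 / 3, P(0) held at 0.58, 1,000 trials each.

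| Analysis | Ratio 0.7 | Ratio 0.5 |
|---|---|---|
| ANOVA, three overlapping windows | 19 / 23 / 30% | 47 / 60 / 70% |
| ANOVA, non-overlapping windows | 13 / 16 / 22% | 34 / 47 / 58% |
| t-test on months 0–12 | 26 / 23 / 18% | 69 / 66 / 57% |
| Negative binomial, months 0–12, unadjusted | 27 / 25 / 21% | 71 / 69 / 61% |
| Negative binomial, months 0–12, baseline-adjusted | 31 / 34 / 41% | 75 / 84 / 88% |

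On the same unadjusted counts, the negative binomial model beats the t-test by only 1 to 4 points. With no true effect, the three-window ANOVA rejected in 4% to 5% of trials and the adjusted negative binomial model in about 6%, so the latter's advantage is slightly overstated.

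**The case against.** **Does the ANOVA sentence cover falls at all?** It opens with balance performance, so it can be read as confined to balance measures, and a statistical analysis plan that is not shown could specify a count model. This stands as a caution. Against it, the sentence goes on to name the secondary outcomes, falls are one of them, and no other group comparison is given for them. The recall-window fault does not depend on this sentence.

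**Is the skewed count with many zeros the cause of the lost power?** A reader might infer this, but the calculations do not support it. Least squares on the raw counts does as well as the negative binomial model once both adjust for baseline falls.

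**Does the overlap itself waste power, or blur the falls effect throughout?** Neither inference holds. Under ANOVA, separate windows had less power than the overlapping ones, and dilution is confined to month 6. Nor is there a false-positive problem.

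**Is the consequence modest?** Yes. Falls are secondary, the stated objective is balance, and at a rate ratio of 0.7 even the better model reaches only 31% to 41%.

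**Conclusion.** The point holds in a limited form. As written, the 6-month falls count is half pre-randomisation, and a true rate ratio of 0.6 would show as about 0.8 at the end of the programme. This rests on an even fall rate and on an effect that begins at baseline. Anyone lost before month 12 has no falls count for months 0 to 6 alone. The 12-month count is sound in this respect.

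If the ANOVA sentence includes falls, which is its most natural reading, power falls by about 13 points at a rate ratio of 0.6 (56 - 43) and 21 points at 0.5 (81 - 60), compared with an analysis that adjusts for baseline falls. The mean, dispersion and rate ratios are assumptions. The direction was the same in every scenario tried, but the size varies with them. The harm is a diluted 6-month estimate and lost power for a secondary outcome. It does not touch the primary comparison or the validity of the test under no effect.

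**What to change.** Make two changes together.

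1. At 6 and 12 months, ask about falls since the last assessment. Keep the 12-month recall at baseline. The follow-up windows then lie wholly after baseline and do not overlap, and a participant lost after month 6 still contributes months 0 to 6.
2. State that falls are not covered by the repeated measures ANOVA. Analyse post-randomisation falls by negative binomial regression with group as the effect, the baseline 12-month count as covariate whether or not the groups differ on it, and log observation time as offset. Report a rate ratio with 95% CI.

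The first change alone would not help under ANOVA, where separate windows had lower power. Baseline-adjusted ANCOVA would recover nearly all the power. The reasons to prefer the count model are the offset for unequal follow-up and a result expressed as a rate ratio.

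The cost is one reworded question at two existing visits and a sentence of analysis text, with no added visits or participants. The downside is that baseline and follow-up recall periods differ in length. The offset handles observation time after baseline, and the baseline count serves only as a covariate. The recall change must be made before the 6-month assessments.

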### Sample Size

Power analysis was based on data from a recent study of community dwelling older people with mild balance impairment (approximately 15–25% impairment compared to healthy controls), which is in the approximate range of impairment anticipated in our sample with mild-moderate severity Alzheimer's disease. Using data from one of the main force platform measures of balance (Limits of Stability, Maximum Excursion, mean score 71.9; SD 14.3) and a clinical balance measure (Step Test, mean score 14, SD 3.6), power calculations were performed to determine the required sample size to demonstrate a 10% improvement, at 80% power and alpha = 0.05. Using these two tests as primary outcome measures for evaluating the effectiveness of the balance retraining exercise programme, a sample size of 80 per group will be required (160 overall). Assuming a loss to follow up of 25%, a sample of 214 will be required for the main study (RCT study). For the longitudinal sub-study, based on the estimated magnitude of balance impairment (15–25%) relative to healthy age matched controls from previous studies, a sample size of 42 will be sufficient to demonstrate group differences (healthy vs Alzheimer's disease group) on the Limits of Stability Maximum Excursion outcome. Allowing for 20% dropout in this group/year over the 2 year follow-up period for this group, 64 healthy age and gender matched controls (matched to the first 64 participants in the control group) will be required for the longitudinal follow-up component of the study. This sample size will be sufficient to identify significant decline in performance over a two year follow-up period (power 0.8, alpha 0.05, single sided analysis, assuming 7% decline in balance performance/year in the Alzheimer's disease group). Previous studies have shown a change of 1–2% per year on balance and mobility measures for healthy older people [58], and over 10% decline in Activities of Daily Living (including locomotion) in six months in people with moderate severity dementia [59].

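### Covariates are chosen by observed baseline imbalance, so the primary model is not fixed in advance and adjustment for the baseline LOS or Step Test score is not guaranteed

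*Protocol article*

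**What the plan says.** The Statistical Analysis section of the protocol article sets one approach for both primary outcomes (LOS Maximum Excursion and Step Test) and for the secondary outcomes: "repeated measures ANOVA between the two groups", "with variables differing between groups at baseline being used as covariates". It names no covariate, gives no candidate list, and does not say how a difference is to be judged. It also does not say whether the baseline score is one of the repeated time points or whether only the follow-up scores are.

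Two other sections bear on this. Under Randomization: "After baseline assessment, participants will be randomly allocated into the exercise or control groups". Under Follow Up Assessments: "Six months after the initial assessment all participants will have all baseline measures repeated by an assessor blind to group allocation", with a further round at 12 months. So every participant has a baseline LOS and Step Test score, taken before allocation on the same instruments as the outcome. No other section overrides the covariate rule.

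**The concern.** Groups formed by random allocation differ at baseline only by chance. The size of a chance difference says nothing about how strongly a variable predicts the outcome, and prediction is what makes a covariate worth including. A rule driven by imbalance can admit a weak predictor that differs by luck and leave out a strong one that looks balanced. The obvious strong candidate is the baseline score on the outcome itself.

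Two things are at stake. One is power: precision available from data already planned is used only when chance triggers it. The other is that the primary model is not fixed. Because neither the candidates nor the meaning of a difference is defined, two analysts following the same sentence could defend different models.

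This is a rule that the article states, not a detail left to an unseen analysis plan. A plan that followed it would carry the weakness forward.

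**Working it through.** **Inputs from the Sample Size section.** LOS: "Limits of Stability, Maximum Excursion, mean score 71.9; SD 14.3". Step Test: "Step Test, mean score 14, SD 3.6". Target: "to demonstrate a 10% improvement, at 80% power and alpha = 0.05". The differences are 7.19 for LOS (7.19/14.3 = 0.503 SD) and 1.4 for the Step Test (1.4/3.6 = 0.389 SD), with 80 per group before dropout.

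**Assumptions, because the article does not give them.** Imbalance is judged at p<0.05; r, the baseline to 6-month correlation, is 0.5 to 0.8; the RCT test is two-sided at 0.05.

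**The plan's own figure.** n per arm = 2(z_alpha + z_0.80)² (SD/difference)².
- Step Test: one-sided 2 × 6.18 × 6.61 = 82; two-sided 2 × 7.85 × 6.61 = 104.
- LOS: one-sided 49; two-sided 63.
- Dropout: 160/0.75 = 213.3, so 214.

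The 80 per group is approximately reproduced only as a one-sided Step Test calculation. The article does not state sidedness for the RCT; that is a separate matter, and two-sided is used below.

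**Power without any selection.** Power = Φ(difference / (SD √(2f/80)) − 1.96), where f = 1 for follow-up scores, 2(1−r) for change scores (the group-by-time test when baseline is a time level), and 1−r² with baseline as a covariate.
- Step Test, f = 1: 1.4/0.569 = 2.46, and Φ(0.50) = 0.69.
- Step Test, covariate: r=0.5, Φ(2.46/0.866 − 1.96) = 0.81; r=0.7, Φ(2.46/0.714 − 1.96) = 0.93; r=0.8, Φ(2.46/0.600 − 1.96) = 0.98.
- Step Test, change score: 0.69, 0.89 and 0.97 at r = 0.5, 0.7 and 0.8.
- LOS, f = 1: 7.19/2.261 = 3.18, and Φ(1.22) = 0.89. With the covariate at r=0.5: Φ(3.18/0.866 − 1.96) = 0.96.

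**Power under the rule.** Trials were simulated with 80 per arm, normal scores and one follow-up. The baseline score was added as a covariate only when its own between-group test gave p<0.05, which happened in about 5% of trials. A range is shown where repeat simulations differed.

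| Step Test | r=0.5 | r=0.7 | r=0.8 |
|---|---|---|---|
| Rule, follow-up scores compared | 0.70 | 0.70–0.71 | 0.70–0.72 |
| Rule, baseline as time level | 0.70 | 0.89–0.90 | 0.97–0.98 |
| Baseline always a covariate | 0.81 | 0.93 | 0.98 |

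For LOS at r=0.5, the rule gives about 0.90 against 0.96 under either reading.

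**Type I error under the rule.** In 8,000 simulated null trials per setting, it was 0.045, 0.039 and 0.030 (r = 0.5, 0.7, 0.8) when follow-up scores are compared, and 0.048 to 0.049 when baseline is a time level. Across all runs the range was about 2.5% to 5%.

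**How often chance alone changes the model.** With k independent candidates tested at 0.05, the chance that at least one is flagged is 1 − 0.95^k: 40% for k=10, 64% for k=20, 79% for k=30. Independence is a simplification, since the balance measures are surely correlated.

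**The case against.** The strongest reply is that a repeated measures ANOVA may already use the baseline score. If baseline is a time level, the group-by-time test acts on change from baseline. The loss against a pre-specified covariate is then about 3 to 4 points at r=0.7 and close to nothing at r=0.8. This stands: the large loss at r=0.7 belongs only to the reading in which follow-up scores are compared, and the text does not settle which applies. It does not remove the loss of about 11 points at r=0.5, which is the same under both readings.

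A reader might also infer four stronger things that the article does not support.
- *That baseline adjustment is given up.* It is conditional, and may also occur through the time factor. It is not guaranteed, which is a weaker statement.
- *That covariates are picked post hoc to suit the result.* The rule is written in advance and looks only at data collected before allocation. It gives no licence to choose by outcome.
- *That false positives increase.* The simulated error rates are at or below 5%.
- *That using the baseline score both as a repeated outcome and as a covariate invalidates the test.* With two time points and a covariate-by-time term, the group-by-time test is a regression of change on group and baseline. That gives the same group test as ANCOVA.

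Finally, the 5% selection rate follows from the assumed p<0.05 criterion; it is not a fact about this protocol.

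**Conclusion.** The point holds as a should-fix. The stated rule lets chance imbalance decide the covariates for both primary outcomes, leaves the model open until baseline data are seen, and does not secure adjustment for the most relevant baseline score. No bias or inflated error is shown, so it is not a must-fix.

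The power loss for the Step Test is about 11 points at r=0.5. At r=0.7 it lies between about 3 and 23 points, depending on how the ANOVA treats baseline. At r=0.8 it runs from almost none to about 26 to 28 points. LOS loses less, about 6 points at r=0.5. These figures rest on the assumed p<0.05 criterion, the assumed range of r, a two-sided test, and a single 6-month comparison with no other covariates.

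The loss matters most for the Step Test, where 80 per arm gives only 0.69 two-sided power unadjusted. With its baseline value always in the model, the number per arm for 80% power falls from 104 to 104 × 0.75 = 78 at r=0.5 and 104 × 0.51 = 53 at r=0.7.

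**What to change.** Delete the imbalance rule from the Statistical Analysis section. State instead that each outcome is analysed with its own baseline value as a covariate, whatever the observed imbalance, and say how the repeated measures model treats the baseline assessment. Name any further covariates in advance as a short list drawn from measures already collected at baseline, such as the MMSE. If adjustment for observed imbalance is still wanted, label it a sensitivity analysis.

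The cost is about one sentence, with no extra participants, visits or measurements. The change should be made before baseline data are examined by group, so that the new list is not itself shaped by the imbalance.
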